### Secondary outcome measurement

#### Visual analogue scale

A visual analogue scale (VAS) is a 10-point scale selected to quantitatively measure the level of low back pain during the study, for which 0 means “none of pain” while 10 represent “the unbearable pain [37]”. It has been proved to have validity and reliability for outcome measurement. We will assess the VAS with a repeated longitudinal analysis.

#### Short-Form Health Survey

The association between health-related quality of life and various factors will be assessed by using the 36-item Short Form Health Survey (SF-36), which includes 36 questions divided into 9 areas. It consists of vitality (4 items), physical functioning (10 items), bodily pain (2 items), general health (5 items), physical role (4 items), emotional role (3 items), social functioning (3 items), mental health (5 items), and health transition (5 items). For each field, scores range from 0 to 100, with higher scores reflecting a better quality of life. A repeated longitudinal analysis will also be used to evaluate the SF-36.

#### Safety evaluation

Adverse events refer to the unexpected responses that occur during or after treatment, which can lead to a hospitalization or even threaten life. The trial should be suspended and immediate process is indispensable whenever we encounter adverse events. Also, we should record the details in the case report forms (CRFs). The efficacy and safety of the intervention will be evaluated with 6 months of unsupervised follow-up, during which the subjects should only be received routine lumbar care. At month 6 and 9, participants will be contacted with the phone for their physical condition of low back pain currently. In addition, evaluators can be reformed 13 with the clinical symptoms and AEs whenever the patients meet something important.

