### Dropout and suspension criteria

Patients have the right to withdraw for any reason during the study period according to the Patient Management Protection Rules. The following conditions are considered as withdrawal criteria: (1) patient does not implement the protocol treatment on schedule; (2) participation in other treatments during the trial; (3) intolerable adverse events; and (4) lost to follow-up. In addition, if severe poor efficacy or adverse reactions occur during the trial, the trial will be forcibly suspended immediately.

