### Interventions

The participants will receive a total of 24 treatments in 3 months. The therapists must have 10 years of experience with Tuina treatment or be skillful in health care education for the participants. In addition, they are required to have passed a clinical test to make sure that the consistency of the trial is administered. It should be emphasized that some other treatments for low back pain during the trial will be forbidden, which includes medication therapy, surgery, drug injections, acupuncture, moxibustion, and physical therapy. If the subjects receive any other treatment, it will be recorded the changeable each time he arrives.

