#### Data collection and monitoring

The screeners will collect data on the baseline characteristics when the patients are recruited, and CRFs will be completed with the outcome measurement by the assessor. This consists of questionnaire-based assessment of treatment effects, lumbar physiological function, adverse events, and safety evaluations. Then two data administrators, who are beyond the research team and blinded to group allocation, will independently receive the completed CRFs and enter them into an Excel database (Microsoft, Redmond, WA, USA). They are required to have completed rigorous training for the data monitoring. Then they will entry the real-time data in the Chinese Clinical Trial Registration Center, in which the electronic data management system will be used to track and monitor the test data in real-time in the Department of Science and Technology in Yueyang Hospital.

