#### Statistical analyses

The intention-to-treat principle will be followed in the primary data analysis with IBM SPSS Statistics for Windows version 21.0 software by statisticians who are blinded to the group allocation. The baseline characteristics will be expressed with descriptive statistics for the two groups, which are reported as the mean ± standard deviation. A Kolmogorov-Smirnov test with Lilliefors correction will be used to analyze all quantitative variables to determine whether they follow a normal distribution. Parametric statistics (Tukey test) or nonparametric statistics (Wilcoxon rank-sum test) will be used for the within- and between-group analyses in accordance with the results of the homogeneity and normality analyses. When initial homogeneity and normality of data distribution are found, repeated measures analysis of variance (ANOVA) and ANOVA with Bonferroni *post hoc* statistics will be used to analyze within and between groups. The Friedman test and Kruskal-Wallis test will be used when initial homogeneity but not normality of data distribution is found. If the initial homogeneity is not found, a linear mixed model will be adjusted for the baseline value. Adverse events in each group will be documented as percentage for safety assessments using the chi-square test or Fisher’s exact test. The statistical significance is defined as *P* < 0.05, and the 95% confidence interval will be reported.

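### Read literally, the only definition of an adverse event leaves minor or expected harms of manipulation out of the between-arm safety comparison

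*Protocol article*

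**What the plan says.** The Safety evaluation section of the protocol article holds the only definition: "Adverse events refer to the unexpected responses that occur during or after treatment, which can lead to a hospitalization or even threaten life". It continues: "The trial should be suspended and immediate process is indispensable whenever we encounter adverse events". For follow-up it adds that "evaluators can be reformed 13 with the clinical symptoms and AEs whenever the patients meet something important".

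The same term is used in three other places.

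- **Statistical analyses:** "Adverse events in each group will be documented as percentage for safety assessments", by chi-square or Fisher's exact test. No other safety variable is tested.
- **Data collection and monitoring**, on the content of the case report form: "This consists of questionnaire-based assessment of treatment effects, lumbar physiological function, adverse events, and safety evaluations".
- **Dropout and suspension criteria:** an individual patient is withdrawn for "3) intolerable adverse events", while "if severe poor efficacy or adverse reactions occur during the trial, the trial will be forcibly suspended immediately".

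The abstract plans a safety evaluation after every session in both arms and names safety as an aim. The Discussion says that the safety of Tuina still needs clinical proof.

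**The concern.** An adverse event is normally any untoward occurrence, and seriousness and expectedness are graded afterwards. Here both qualifiers are built into the basic term. The result resembles a definition of an unexpected serious event, and that term then feeds the only between-arm safety test.

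The harms most likely to separate these two arms are minor and foreseeable. The Interventions section states: "The participants will receive a total of 24 treatments in 3 months". In the Tuina arm each session involves elbow or thumb pressure and lumbar rotation carried to its limit. The education arm receives a presentation, a booklet, a video and individual talks. If minor physical effects are not adverse events, both arms may report close to none, and a reader could take this as evidence of equal safety.

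**Working it through.** The protocol states no event rate or safety power, so there is no figure to reproduce. The point rests on wording. The arithmetic below only illustrates what is at stake.

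**Step 1: apply the definition to a minor, foreseeable event** such as soreness after manipulation.

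| Reading of the definition | Is the event counted? |
|---|---|
| Literal: unexpected, and able to lead to admission or threaten life | No, on both counts |
| The clause on hospitalisation is only descriptive; *unexpected* keeps its usual meaning | No, because it was foreseeable (an unforeseen minor event would count) |
| The clause is descriptive and *unexpected* loosely means untoward | Yes |

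The literal reading excludes minor harms. Only the loosest reading counts all of them.

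**Step 2: look for a passage that widens the term.**

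- The withdrawal criterion on intolerable events implies tolerable ones, which is hard to reconcile with a life-or-hospital threshold. It shows tension but does not redefine anything.
- The case report form lists safety evaluations beside adverse events, so more may be recorded. The test in Statistical analyses still names adverse events alone.
- The evaluation after each session gives the occasion to record minor harms but no rule that they count.

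**Step 3: illustrate the size.** Inputs: 80 patients per arm (Sample size calculation), two-sided 0.05 (the level is from Statistical analyses; two-sided is assumed), and minor-harm rates per patient, all assumed.

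Tuina patients uncounted = 80 × rate: 80 × 0.05 = 4; 80 × 0.10 = 8; 80 × 0.20 = 16.

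Two-sided Fisher test: 8/80 v 1/80 gives p = 0.034; 4/80 v 1/80 gives p = 0.37. If those events are not counted, the table could be 0/80 v 0/80 or 1/80 v 0/80, and p = 1.0 for either.

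Exact Fisher power if every event is counted:

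| Tuina v education (assumed) | Power |
|---|---|
| 5% v 1% | 11% |
| 10% v 1% | 62% |
| 20% v 1% | 99% |
| 10% v 5% | 14% |
| 20% v 5% | 79% |

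**Step 4: check what a wider definition would do to the suspension sentence.** If every event of any kind triggered suspension, the chance that 160 patients finish without a trigger is (1 − p₁)^80 × (1 − p₂)^80:

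- 1% v 1%: 0.99^80 × 0.99^80 = 0.20
- 5% v 1%: 0.95^80 × 0.99^80 = 0.0074

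So the definition cannot be widened without also changing the suspension rule. These two figures describe an incomplete correction; they are not a forecast for the plan as it stands.

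**The case against.** The strongest reply is that the English is loose and the intent was broader. The protocol lists no expected reactions and has no expectedness assessment, so *unexpected* may simply mean untoward. The withdrawal criterion, the separate safety evaluations on the case report form and the check after each session all point the same way. This stands as evidence of intent. It rules out the stronger claim that minor harms are excluded on every possible reading. It does not repair the text, because nothing else redefines the term and the test uses that term only.

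A reader might also infer that the two suspension rules flatly contradict each other. The document does not support that. In Dropout and suspension criteria, *severe* may govern adverse reactions as well as poor efficacy. If it does, and the definition under Safety evaluation is a seriousness threshold, both rules suspend for serious harm. What remains is an ambiguity of scope.

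Nor should the worst cases be added together. On the literal reading minor events go uncounted but do not stop the trial. On the looser readings the minor events that could stop it are also counted.

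It would also be wrong to say that adverse events in follow-up go unreported, since patient-initiated reports are allowed.

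Finally, a journal article may leave grading and reporting procedures to the full protocol. That is fair for such detail. It does not cover a definition that the article itself states.

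**Conclusion.** The point holds as a defect of wording with a real consequence for a stated aim. Followed literally, the plan omits minor or expected harms of manipulation from its only between-arm safety comparison, and the definition does not match the way the withdrawal criteria use the same term.

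The omission probably favours Tuina, on the assumption that minor physical effects arise mainly in the manipulated arm. That direction is inferred from the procedures. The size is unknown: the 4, 8 or 16 uncounted patients and the power range of 11% to 99% depend wholly on assumed rates and on the literal reading. The trial was not sized for safety, and at 5% v 1% the test would have only 11% power even with complete counting. The gain there would be mainly honest percentages by arm.

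This should be fixed, but it does not threaten the primary Oswestry Disability Index comparison.

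**What to change.** 1. **Safety evaluation, definition.** Replace it with: *An adverse event is any untoward occurrence in either arm during or after treatment, whether or not it is expected, serious or related to treatment. A serious adverse event is one that leads to hospitalisation or threatens life.*
2. **Recording.** Enter all events at the safety evaluation already planned after each session.
3. **Statistical analyses.** Run the stated test on patients with at least one event of any kind, and report serious events separately by arm.
4. **Suspension.** Limit it to serious adverse events under Safety evaluation. In Dropout and suspension criteria, write *severe poor efficacy or serious adverse events*, which also settles the scope of *severe*. This has to go with item 1.

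The cost is a few sentences, slightly more recording, and reported rates that may look less favourable. Recruitment began in June 2019, so minor events in patients already treated may be only partly recoverable. The report should say from what date the wider definition applied.

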#### Data collection and monitoring

The screeners will collect data on the baseline characteristics when the patients are recruited, and CRFs will be completed with the outcome measurement by the assessor. This consists of questionnaire-based assessment of treatment effects, lumbar physiological function, adverse events, and safety evaluations. Then two data administrators, who are beyond the research team and blinded to group allocation, will independently receive the completed CRFs and enter them into an Excel database (Microsoft, Redmond, WA, USA). They are required to have completed rigorous training for the data monitoring. Then they will entry the real-time data in the Chinese Clinical Trial Registration Center, in which the electronic data management system will be used to track and monitor the test data in real-time in the Department of Science and Technology in Yueyang Hospital.

#### Statistical analyses

The intention-to-treat principle will be followed in the primary data analysis with IBM SPSS Statistics for Windows version 21.0 software by statisticians who are blinded to the group allocation. The baseline characteristics will be expressed with descriptive statistics for the two groups, which are reported as the mean ± standard deviation. A Kolmogorov-Smirnov test with Lilliefors correction will be used to analyze all quantitative variables to determine whether they follow a normal distribution. Parametric statistics (Tukey test) or nonparametric statistics (Wilcoxon rank-sum test) will be used for the within- and between-group analyses in accordance with the results of the homogeneity and normality analyses. When initial homogeneity and normality of data distribution are found, repeated measures analysis of variance (ANOVA) and ANOVA with Bonferroni *post hoc* statistics will be used to analyze within and between groups. The Friedman test and Kruskal-Wallis test will be used when initial homogeneity but not normality of data distribution is found. If the initial homogeneity is not found, a linear mixed model will be adjusted for the baseline value. Adverse events in each group will be documented as percentage for safety assessments using the chi-square test or Fisher’s exact test. The statistical significance is defined as *P* < 0.05, and the 95% confidence interval will be reported.

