### Outcome measurements

The outcome will be measured by three self-report questionnaires, which can reflect the lumbar dysfunction, pain, and quality of life. Six time points will be used to assess outcomes, including baseline (after enrollment); months 1, 2, and 3 (intervention session); and months 6 and 9 (follow-up sessions).

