### Primary outcome measurement

#### Oswestry Disability Index

The primary outcome is the subject’s perceived disability, which is assessed by the modified Oswestry Disability Index (ODI) [36]. The ODI consists of ten items, including pain intensity, personal care, lifting, walking, sitting, standing, sleep, sex life, social life, and traveling. According to the extent of disability, each item is scored from 0 to 5. The total score is reported as a percentage, which is actual score/50 (maximum possible score) × 100%. The ODI results will be assessed using a repeated longitudinal analysis.

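### The rank-sum test, a test for independent samples, is named for within-group comparisons of the same patients, and the paragraph does not say whether this rule or its related-samples methods govern

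*Protocol article*

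**What the plan says.** The Statistical analyses section first gives a general rule that depends on homogeneity and normality: "Parametric statistics (Tukey test) or nonparametric statistics (Wilcoxon rank-sum test) will be used for the within- and between-group analyses".

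It then gives a second rule, again split by homogeneity and normality:

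- Homogeneous and normal: "repeated measures analysis of variance (ANOVA) and ANOVA with Bonferroni" post hoc statistics, for analyses within and between groups.
- Homogeneous but not normal: "The Friedman test and Kruskal-Wallis test will be used when initial homogeneity but not normality of data distribution is found".
- Not homogeneous: "If the initial homogeneity is not found, a linear mixed model will be adjusted for the baseline value".

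The Outcome measurements section fixes the data structure: "Six time points will be used to assess outcomes, including baseline (after enrollment); months 1, 2, and 3 (intervention session"; the list continues with months 6 and 9. For the primary outcome the article adds: "The ODI results will be assessed using a repeated longitudinal analysis". The same is said of the VAS and the SF-36. No signed-rank test, paired t test or other paired two-visit test is named anywhere.

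**The concern.** A within-group comparison asks whether the same patients differ between two visits. The rank-sum test obtains its null distribution by treating the two sets of scores as unrelated samples. When a patient's scores at the two visits are positively correlated, as one would expect for disability, pain and quality-of-life scores, that null variance is too large and the test rejects too rarely.

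This is more than detail left to a fuller document: the article names a specific test for a specific purpose, and the test does not suit it. The paragraph also gives two overlapping rules for within-group analysis, one with an independent-samples test and one with related-samples methods. At stake is a modest real change within an arm being reported as non-significant and then read as no change.

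**Working it through.** **Plan's own figure.** The plan gives no figure for within-group comparisons, so there is none to reproduce. The sample size rests on between-group response rates and does not bear on this point.

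**Inputs from the article.** 80 patients per group; up to 10% dropout, so 80 × 0.9 = 72; significance at 0.05 (sidedness not stated, two-sided taken here).

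**Assumed inputs.** The article gives no within-patient correlation, SD or expected change. I take a correlation ρ of 0.3, 0.5 and 0.7, and a change of 0 to 0.8 SD.

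**Step 1, true level by large-sample approximation.** With paired data and no change, the variance of the rank-sum statistic is about (1 − ρ_S) times the value the test assumes, where ρ_S is the Spearman correlation. For bivariate normal scores ρ_S = (6/π)·arcsin(ρ/2). The nominal cut-off of 1.96 then acts as 1.96/√(1 − ρ_S).

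| ρ | ρ_S | effective cut-off | true two-sided level |
|---|---|---|---|
| 0.3 | 0.288 | 1.96/√0.712 = 2.32 | 2.0% |
| 0.5 | 0.483 | 1.96/√0.517 = 2.72 | 0.6% |
| 0.7 | 0.683 | 1.96/√0.317 = 3.48 | 0.05% |

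**Step 2, true level by simulation.** Bivariate normal scores at two visits, n = 80, 4000 runs per setting:

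| ρ | rank-sum | signed-rank |
|---|---|---|
| 0.3 | 2.5% | 5.6% |
| 0.5 | 0.7% | 5.1% |
| 0.7 | 0.05% | 4.7% |

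These agree with Step 1 within simulation error. A repeat with 20,000 runs gave 2.1%, 0.7% and 0.1% for rank-sum.

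**Step 3, power by simulation**, n = 80, rank-sum against signed-rank:

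| ρ | 0.3 SD | 0.5 SD | 0.8 SD |
|---|---|---|---|
| 0.3 | 44% vs 58% | 91% vs 96% | 100% vs 100% |
| 0.5 | 44% vs 74% | 94% vs 99% | 100% vs 100% |
| 0.7 | 42% vs 91% | 97% vs 100% | 100% vs 100% |

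At 0.3 SD the loss runs from about 15 to about 49 points. At 0.5 SD it is about 3 to 5 points here; separate runs put it at up to 6. At 0.8 SD there is none. With 72 patients per arm the pattern is the same, with somewhat larger losses at 0.5 SD (about 5 to 9 points).

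**Step 4, boundary check.** At ρ = 0 and n = 80 the two tests perform alike: level 5.0% against 5.1%, and power 79% against 78% at a change of 0.453 SD. The loss therefore comes from ignoring the pairing.

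**The case against.** The strongest reply is that the rank-sum sentence is a general one and that related-samples methods follow at once for every branch: repeated measures ANOVA, Friedman and the mixed model. The abstract and the outcome sections also promise a repeated-measures or longitudinal analysis. That much stands. A reader might infer that paired visits will be analysed as two separate samples, but the text does not settle this. It leaves two rules unreconciled. The later methods do not remove the problem, because nothing says that they replace the earlier sentence. Friedman is also an overall test that does not show which visits differ, and Bonferroni is attached only to the ANOVA branch. Equally, the article does not say that pairwise visit contrasts will be run on non-normal data, and it names no contrast of month 3 with month 6 or 9. Post hoc detail may stand in a fuller plan.

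Other stronger readings also lack support:

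- That real change would be missed far more often in general. This depends on an assumed correlation and a small change, and it disappears for large changes.
- That the 95% intervals would be too wide. The article promises intervals but gives no method for them.
- That the Tukey test would carry an independent-groups error term. No error term is stated, and Tukey comparisons can use a within-subject one.
- That the main result is at risk. The aim is to compare Tuina with education, for which the rank-sum test suits independent groups. The error is also conservative, so it does not create false claims of change.

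**Conclusion.** The point holds in limited form. The article names an independent-samples test for within-group analysis of repeatedly measured patients, and it does not say whether that sentence or the related-samples methods after it govern. If the rank-sum sentence were followed for two-visit comparisons, the true level would be about 2 to 2.5% at a correlation of 0.3, about 0.7% at 0.5, and about 0.1% or less at 0.7. Power would suffer materially for changes of about 0.3 SD, slightly at 0.5 SD, and not at all at 0.8 SD. These sizes rest on assumed correlations and changes, normal scores and two-sided testing. That the named test is wrong for paired visits does not depend on those assumptions. The consequence is confined to within-group statements.

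**What to change.** In the Statistical analyses section:

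1. Limit the Wilcoxon rank-sum test to between-group comparisons.
2. For within-group comparisons of two visits, name the Wilcoxon signed-rank test, or contrasts from the repeated-measures or mixed model already planned. State that Bonferroni correction applies to these comparisons too; at present it is tied only to the ANOVA branch.
3. State which sentence governs the within-group analysis, so that the general rule and the branch-specific rules no longer overlap.

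The cost is a sentence or two of wording, settled before the data are analysed. No patients, visits or data are added.

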**Methods/design:**

This study is a randomized controlled trial with parallel-group design including two groups: a Tuina group and a health care education group. A total of 160 eligible participants will be randomly assigned to the groups in a 1:1 ratio. The interventions of both groups will last for 20 min and be carried out twice each week for a period of 12 weeks. The primary outcome is the Oswestry Disability Index. The secondary outcomes include a visual analogue scale and the 36-item Short Form Health Survey. They will be assessed at baseline, at the end of the intervention every month, and during 6 months and 9 months of follow-up by repeated measures analysis of variance. The significance level is 5%. The safety of Tuina and health care education will be evaluated after each treatment session. This study will focus on the value of Tuina and health care education for low back pain and will highlight any differences in the efficacy of the treatments.

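### The primary ODI analysis is chosen by pre-tests on the trial data, with baseline adjustment in only one branch, so neither the test nor the estimand is fixed

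*Protocol article*

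**What the plan says.** The Statistical analyses section of the protocol article sets out a decision rule. All quantitative variables are first tested for normality (Kolmogorov-Smirnov with Lilliefors correction). If *initial homogeneity* and normality are both found, repeated measures ANOVA with Bonferroni post hoc tests is used. The second branch reads: "The Friedman test and Kruskal-Wallis test will be used when initial homogeneity but not normality of data distribution is found". The third reads: "If the initial homogeneity is not found, a linear mixed model will be adjusted for the baseline value". No test or threshold for initial homogeneity is given.

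The same section has another, overlapping rule: "Parametric statistics (Tukey test) or nonparametric statistics (Wilcoxon rank-sum test) will be used for the within- and between-group analyses", again depending on the pre-test results.

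Two other places describe the ODI analysis. Under Oswestry Disability Index: "The ODI results will be assessed using a repeated longitudinal analysis". The abstract names a single method without conditions: outcomes are assessed at baseline, monthly during treatment and "during 6 months and 9 months of follow-up by repeated measures analysis of variance". The Outcome measurements section lists six assessment times: baseline and months 1, 2, 3, 6 and 9.

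**The concern.** This is a stated rule, not a detail left to a later analysis plan. Under it, the trial data decide which hypothesis about the primary outcome is tested and whether baseline ODI enters the analysis. The branches do not answer the same question, so the meaning of the primary P value is unknown until the data are seen.

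Baseline ODI is collected on every patient and would normally improve precision whether or not the groups happen to differ. The rule keeps explicit adjustment for the case where homogeneity fails, which randomisation makes uncommon. At stake are a fixed primary estimand and some power.

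**Working it through.** **1. The three descriptions side by side.** The abstract gives unconditional repeated measures ANOVA. The ODI section gives an unnamed longitudinal analysis. The Statistical analyses section makes ANOVA one of three conditional routes. Neither of the first two settles the third.

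**2. What each branch tests.**
- Repeated measures ANOVA: group, time and group-by-time terms. The article does not say which is primary.
- Friedman: change over time within one group only. Kruskal-Wallis with two groups: a rank-sum comparison that uses neither time nor baseline. This branch does not test the longitudinal group effect.
- Mixed model: a baseline-adjusted group effect.

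**3. How often adjustment would apply.** Read initial homogeneity as baseline comparability, tested at P<0.05. Under randomisation that test rejects in 5% of trials, so 100% − 5% = 95% go without the stated adjustment.

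**4. Power.** The plan has no ODI power figure to reproduce: its sample size rests on rates of 95% and 85%, not on ODI. Inputs:
- n = 80 × (1 − 0.10) = 72 per arm (Sample size calculation).
- Difference d = 0.4 SD: assumed.
- Baseline-outcome correlation ρ = 0.3, 0.5, 0.7: assumed.
- Normal data, two-sided 5%.

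For one visit, power ≈ Φ(d√(n/2)/s − 1.96), with d√(n/2) = 0.4 × 6 = 2.4.
- Unadjusted, s = 1: Φ(0.44) = 67%.
- Always adjusted, s = √(1 − ρ²) = 0.954, 0.866, 0.714: Φ(0.56), Φ(0.81), Φ(1.40) = 71%, 79%, 92%.

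For the ANOVA group-by-time test, take six visits with baseline as a time level, equal correlation between visits and a constant effect after baseline. The noncentrality is (n/2)d²(5/6)/(1 − ρ) = 4.8/(1 − ρ) = 6.9, 9.6, 16.0, on 5 and 710 degrees of freedom. Power is 49%, 65%, 89%.

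Simulation agrees within about a point and adds the conditional rule (adjust only if baseline differs at P<0.05, otherwise compare one visit unadjusted):

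| ρ | Always adjusted | Conditional, single visit | ANOVA group-by-time |
|---|---|---|---|
| 0.3 | 70% | 66% | 49% |
| 0.5 | 78% | 68% | 66% |
| 0.7 | 92% | 69% | 89% |

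The loss is 4, 10 and 23 points on the single-visit reading, and 21, 12 and 3 points on the group-by-time reading. The always-adjusted column is a single-visit contrast, whereas the ANOVA column is a test over all visits.

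If the ANOVA group main effect were the test, at ρ = 0.7 the mean effect is 0.4 × 5/6 = 0.333 and the SD of a patient's mean is √((1 + 5 × 0.7)/6) = 0.866. Power is Φ(0.333 × 6/0.866 − 1.96) = Φ(0.35), about 63% to 64%.

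**5. Type I error.** Simulated for the conditional rule, with and without the Lilliefors step: about 4% to 5% (3.6% to 4.9% across settings). Not inflated.

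**6. Rank-sum test within groups.** Within-group data are paired, but the test assumes independent samples. The true level is roughly 2Φ(−1.96/√(1 − ρ)): at ρ = 0.3, 0.5, 0.7 this is 2Φ(−2.34), 2Φ(−2.77), 2Φ(−3.58) = 1.9%, 0.6%, 0.03%. Simulation gives about 2%, 0.7% and 0.1%, against a nominal 5%.

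**The case against.** The strongest reply is that ANOVA with baseline as one of six time levels already uses baseline through the group-by-time term. A single-visit comparison that ignores baseline is then the wrong yardstick. This stands in part. A reader might infer a loss of 23 points at ρ = 0.7, or that most of the value of baseline ODI is thrown away. On the group-by-time reading the loss there is only about 3 points, and it shrinks rather than grows with correlation. But the article does not say which ANOVA term is primary, and both the main-effect and single-visit readings lose much more at that correlation.

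A reader might also infer that data-driven test selection inflates false positives. The simulations do not support that for this rule. The rank-sum error makes within-group tests conservative and does not touch the randomised comparison.

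The power loss is not universal. With lognormal data, ρ = 0.3 and a difference of 0.467 SD (the one giving 80% power unadjusted), the rule, which then mostly led to the rank test, had 92% power against 83% for baseline-adjusted analysis.

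Initial homogeneity might mean equal variances rather than comparable baselines. The 95% figure would then not apply, but the data would still choose the test and adjustment would still be conditional.

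Two criticisms should not be made. The section promises a 95% confidence interval without saying of what, so the rank branch does not break a promise of a mean difference. And Tukey's test is not without a role, since the sentence naming it covers within-group analyses and there are six time points.

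**Conclusion.** The point holds: as written, the primary ODI test and its estimand are selected by pre-tests on the trial data, one of them undefined, and baseline adjustment is conditional. The rank branch does not test the longitudinal group effect, and the rank-sum test is wrong for paired within-group comparisons.

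The direction of the power loss is clear for normal data. Its size, about 3 to 23 points over the settings tabulated, depends on which term is tested and on an effect size and correlations that the article does not give. With no excess false positives, this is a defect that should be fixed rather than one that invalidates the trial.

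**What to change.** Name one unconditional primary analysis for ODI in all randomised patients: a linear mixed model over months 1, 2, 3, 6 and 9 with group, visit, group-by-visit and baseline ODI. Name one primary contrast in advance, for example the adjusted group difference at month 3 (end of treatment) with its 95% confidence interval. Without that, the model yields five visit contrasts and an omnibus interaction, and the primary P value stays open.

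Use the same model for VAS and SF-36. Remove the normality and homogeneity gate, and keep one rank-based sensitivity analysis. Use the signed-rank test for any paired within-group comparison. Align the abstract and the Oswestry Disability Index section with the new text.

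The cost is wording: the mixed model is already in the plan, and baseline ODI is already collected. The downside is some loss of power if ODI turns out strongly skewed.
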